### Recruitment {15}

A multi-pronged approach is used for recruitment. This includes placement of physical posters across different university campuses and disseminating recruitment advertisements on social media platforms such as Telegram and Facebook. Participants are screened twice to ensure that they meet the inclusion and exclusion criteria of the study. In the first screening round, participants are requested to complete a brief online questionnaire. This questionnaire collects basic screening criteria such as age, sex, nationality, information on pre-existing health condition, and critical MRI contraindications. Experimenters will carefully review responses from the first screening round and invite eligible participants to proceed to the second round of screening,

In the second round of screening, participants are invited to complete a more detailed online screening questionnaire. This questionnaire includes more in-depth health screening questions and the Edinburgh Handedness Inventory [54] to gather additional information on participants’ eligibility. After reviewing responses, eligible participants are recruited in batches and promptly contacted to schedule the first Baseline Cognitive Session. This batch recruitment approach ensures effective management and allocation of available manpower and facilitates the matching of participants into Training and Control groups. Participants who do not meet the eligibility criteria will be informed.

## Assignment of interventions: allocation

### Sequence generation {16a}

The allocation sequence is controlled with an algorithm written in R and we employ variance minimisation procedures [55] to match age, sex, intelligence and cognitive flexibility while randomly allocating participants to either the Training or Control group. Intelligence is assessed using the RAPM score, while cognitive flexibility is assessed through the switch cost in accuracy and reaction time on the CST. Both intelligence and cognitive flexibility measures are collected during the Baseline Cognitive Session. The matching algorithm script is executed only when participants within a recruitment batch have all completed the Baseline Cognitive Session. Data from the previous batches of recruited participants is considered during the group allocation. This approach ensures that the two groups remain matched on pre-specified matching variables with each batch of incoming new participants.

Participant data for each matching measure are first collated into a source Excel file. Group assignment for the first recruitment batch is done sequentially upon initialisation of the algorithm. Once the number of assigned participants reaches the number of groups present, i.e. two in the present study, subsequent participants are temporarily assigned to one group at a time. For each potential group assignment, we compute the mean of each matching measure within each group and thereafter derive a mean of means between groups as well as the sum of squared deviations of this group mean. The end goal of the algorithm is to achieve the best minimal sum of squared deviations of this group mean by exploring all possible group allocation of a particular participant. We ensure a balance group allocation of 1:1 (Training vs. Control) by constraining the algorithm such that it will not assign a new participant to the same group as the previous participant.

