**Methods:**

Participants are pseudo-randomised to either the Training or Control group, while matched on age, sex, intelligence and cognitive flexibility performance. In the Training group, participants undergo around 2 weeks of training (at least 13 sessions) on Structure Learning. In the Control group, participants do not have to undergo any training and are never exposed to the Structure Learning task. The effects of Structure Learning training are investigated at both the behavioural and neural level. We measured covariates that can influence an individual’s training performance before the training phase and outcome measures that can potentially show training benefits after the training phase. At the behavioural level, we investigated outcomes in both cognitive and social aspects with a primary focus on executive functions. At the neural level, we employed a multimodality approach and investigated potential changes to functional connectivity patterns, neurometabolite concentration in the frontal brain regions, and brain microstructure and myelination.

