### Trial design {8}

Participants are recruited in batches consisting of up to 18 individuals. To establish a baseline, each batch of recruited participants undergoes a cognitive session that assesses their verbal and non-verbal intelligence, and baseline cognitive flexibility performance. Following the baseline assessment, participants are assigned to either the (1) Training group (receiving Structure Learning training) or (2) Control group (serving as a passive control without any training) using a parallel assignment method. The allocation ratio is set at 1:1 to ensure an equal distribution of participants between the two groups. Group assignment follows procedures of a randomised controlled trial but with matching constraints of age, sex, intelligence, and baseline cognitive flexibility performance between groups. Measures of executive functions can be susceptible to practice effects which can confound the study outcomes [42]. We circumvent this issue by administering most primary and secondary measures only at the post-test to both Training and Control groups. Therefore, matching the groups in the aforementioned variables is important so that we can compare critical outcome measures of the two groups at post-test to examine the effects of the Structure Learning training programme. Consequently, the study is designed as a superiority trial with the aim of demonstrating that the performance of the Training group that engages in the Structure Learning training programme will be superior to that of the Control group for primary outcome measures administered at post-test.

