### Outcomes {12}

In the present study, multiple behavioural tasks are administered to measure various cognitive constructs. Primary behavioural constructs under investigation include Structure Learning, cognitive flexibility, inhibition, and working memory. Secondary behavioural constructs under investigation include creativity, intelligence, problem-solving, language skills, numeracy skills, social tendencies, and decision making. These measures are conducted only at pre-test assessment, i.e. baseline, only at post-test assessment, i.e. after the end of structure learning training and approximately 2 months from pre-test assessment, or at both pre-test and post-test assessments. Specifically, we administered secondary behavioural constructs measuring language skills, numeracy skills, and intelligence (with the exception of the Raven’s Advanced Progressive Matrices) only at pre-test assessments as they are traits that remain relatively stable across the adult lifespan. We administered primary and secondary behavioural constructs measuring cognitive flexibility (with the exception of the Colour Shape Task), inhibition, working memory, creativity, and problem-solving only at post-test assessments to eliminate possibility of practice effects. Finally, matching tasks, i.e. Colour Shape Task and Raven’s Advanced Progressive Matrices, secondary behavioural constructs that measure social tendencies and decision making (and hence more impervious to practice effects) and all secondary neuroimaging constructs are measured at both pre and post-test assessments. Both the Control and Training groups undergo the same measures at pre and post-test assessments. However, measures for Structure Learning are collected only for the Training group. In addition, we investigate potential neural benefits of the Structure Learning training by assessing secondary neuroimaging outcomes both structurally and functionally. Detailed information regarding the individual tasks used this study can be found in Appendix B in the supplementary information.

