Standardised tests used to measure intelligence (RAPM, WASI Vocabulary, WASI Block Design), language, and numeracy skills (WJIV tasks) are widely validated. The RAPM administered in pre-test and post-test are parallel versions that contain items from Set I and Set II of RAPM [56]. The pre-test and post-test versions have Cronbach’s *a*= 0.59 and 0.64 respectively [57]. No concurrent validity was reported during the construction of Zaaiman et al.’s [57] version of RAPM, but items in both versions were selected using empirical data. Only the vocabulary and block design subtests of WASI-II are administered to measure verbal and non-verbal intelligence respectively. Both subtests have excellent internal reliabilities and high concurrent validity, with Cronbach’s *a*ranging from 0.90 to 0.92 and correlation with other intelligence tests ranging from 0.71 to 0.92 [58]. Lastly, the WJIV tasks also exhibit reliability coefficients ranging from 0.74 to 0.97 and have strong concurrent validity with other tests [59].

Preprocessing will first be performed on rs-fMRI data to enhance quality of data. A standard SPM pipeline (http://www.fil.ion.ucl.ac.uk/spm/software/spm12/, SPM12 v7771) will be employed to model fMRI data. We will reslice the aligned EPI data to 2 × 2 × 4 mm^3^ resolution and apply spatial smoothing with a 6-mm isotropic FWHM Gaussian kernel (SPM smooth). The rs-fMRI noises will be processed by standard denoising pipeline in CONN (https://web.conn-toolbox.org, CONN 21a), including linear detrending, 12 potential motion related noise components, noise components from cerebral white matter and cerebrospinal areas, wavelet despiking. Note that the global signal will not be added as a nuisance regressor as suggested by Murphy and Fox [60]. We also correct for inhomogeneity of the magnetic field by acquiring opposite phase encoded field maps (phase encoded direction A-P and P-A). FSL (version 6.0, using topup function) will be used to preprocess the field maps.

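### Intelligence is matched only on a RAPM version with stated alpha 0.59, so the group comparison should also be adjusted for the more reliable WASI scores already collected

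*Protocol article*

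**What the plan says.** The abstract describes the two groups as "matched on age, sex, intelligence and cognitive flexibility performance". Trial design {8} explains why this matters. To avoid practice effects, most outcomes are measured only after training, so comparability at post-test depends on the matching. Outcomes {12} confirms that inhibition, working memory and every cognitive flexibility task except the Colour Shape Task have no baseline.

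Sequence generation {16a} names one intelligence variable for the algorithm: "Intelligence is assessed using the RAPM score".

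Plans for assessment and collection of outcomes {18a} describes the instruments:
- **RAPM.** "The RAPM administered in pre-test and post-test are parallel versions that contain items from Set I and Set II of RAPM". The alphas of the pre-test and post-test versions are "0.59 and 0.64 respectively". On validity: "No concurrent validity was reported during the construction of" the version used, although its items were chosen from empirical data.
- **WASI Vocabulary and Block Design.** These are the verbal and non-verbal measures, with alpha "ranging from 0.90 to 0.92 and correlation with other intelligence tests ranging from 0.71 to 0.92".

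Outcomes {12} places the WASI subtests at pre-test only, and says: "Both the Control and Training groups undergo the same measures at pre and post-test assessments".

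The Statistical methods section on efficacy plans parametric tests and a multivariate mixed effects model for Training versus Control, and names no baseline covariate. The next section, on training performance and cognitive flexibility, does enter the baseline and pre-test measures as covariates, but that model concerns training performance.

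**The concern.** Balance on an observed score gives balance on the underlying trait only as far as the score is reliable. At alpha 0.59 the score correlates about 0.77 with what it measures (the square root of 0.59). Two groups with equal RAPM means can therefore still differ noticeably in intelligence. Most executive-function outcomes have no baseline of their own to absorb such a difference. The description of the groups as matched on intelligence thus promises more control than the measure can give, while a more reliable intelligence measure, taken before training on the same people, has no stated role in the group comparison.

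**Working it through.** **Inputs from the protocol.** Reliability 0.59 for the pre-test RAPM and 0.90 to 0.92 for the WASI subtests ({18a}); 50 evaluable per group (Sample size {14}).

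**Assumptions.** Alpha is taken as reliability. RAPM and WASI are treated as measuring one shared construct. Balance on the matched score is perfect, which is the best case. True intelligence correlates r = 0.3 to 0.5 with an outcome; the protocol gives no figure for this. The alphas are quoted from cited sources and cannot be recomputed here.

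**Step 1: true intelligence difference left after matching.** In true-score SD units, SD = √[(2/n)(1 − reliability)] with n = 50.

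| Matching score | Calculation | SD | 95% range |
|---|---|---|---|
| None | √(0.04 × 1) | 0.200 | ±0.39 |
| RAPM, 0.59 | √(0.04 × 0.41) | 0.128 | ±0.25 |
| Reliability 0.90 | √(0.04 × 0.10) | 0.063 | ±0.12 |
| Reliability 0.91 | √(0.04 × 0.09) | 0.060 | ±0.12 |
| Reliability 0.92 | √(0.04 × 0.08) | 0.057 | ±0.11 |

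The share of chance variance removed by RAPM is (0.0400 − 0.0164)/0.0400 = 59%.

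A simulation with 60 per group and five matching measures, assigning one of each successive pair to each arm so as to minimise imbalance, gave SDs of 0.120 (reliability 0.59) and 0.066 (0.90). The formula gives 0.117 and 0.058 at that size.

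**Step 2: effect on an outcome.** Multiply the residual SD by r.
- RAPM: 0.128 × 0.3 = 0.04; 0.128 × 0.5 = 0.06 outcome SD.
- Reliability 0.91: 0.060 × 0.3 = 0.02; 0.060 × 0.5 = 0.03 outcome SD.

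For scale, the standard error of an unadjusted 50-per-group difference is √(2/50) = 0.20 SD, and the effect used for planning is d = 0.25.

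**Step 3: value as a covariate.** Residual outcome variance = 1 − r² × reliability.

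| r | RAPM (0.59) | WASI (0.91) | Ratio |
|---|---|---|---|
| 0.3 | 1 − 0.09 × 0.59 = 0.947 | 1 − 0.09 × 0.91 = 0.918 | 1.03 |
| 0.4 | 1 − 0.16 × 0.59 = 0.906 | 1 − 0.16 × 0.91 = 0.854 | 1.06 |
| 0.5 | 1 − 0.25 × 0.59 = 0.853 | 1 − 0.25 × 0.91 = 0.773 | 1.10 |

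WASI in place of RAPM as the intelligence covariate is therefore worth about 3% to 10% more participants.

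**The case against.** **RAPM is a defensible matching variable.** It is given before and after training and is itself an outcome with a change score, so matching on it balances that outcome's baseline. The protocol also reports the weak alpha and the missing validity evidence openly. This stands, and is a reason to leave the algorithm as it is.

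**A reader might infer that both WASI scores were available at allocation and should have replaced RAPM in the script.** The documents do not establish this. Trial design {8} has each batch undergo "a cognitive session that assesses their verbal and non-verbal intelligence, and baseline cognitive flexibility performance" before assignment, but RAPM and Vocabulary alone would satisfy that. Participant timeline {13} lists non-verbal intelligence among the pre-test measures, and the Discussion puts standardised intelligence tests after assignment. Table 3 schedules Pre-Test Cognitive Session 2 (weeks 4–5) after matching (weeks 2–3). The session-by-session task list is in a supplement not shown. In addition, this version is dated 11 May 2023, collection was projected to end in June 2023 and participation lasts 10 weeks, so almost no batches would remain to be allocated.

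**A reader might infer that the groups are balanced mostly on noise, or that the imbalance carries over in full to the primary comparison.** Neither follows. Alpha 0.59 means 59% true variance, and the imbalance reaches an outcome only after multiplication by r. If allocation is random, it is already part of the standard error.

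**The calculation idealises.** It assumes one construct, whereas {18a} assigns Vocabulary and Block Design to verbal and non-verbal intelligence. It also assumes perfect balance, which the rule in {16a} against placing consecutive participants in the same group may prevent. That rule is a separate question; if it weakens the matching, adjustment matters more.

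**Covariates may be named in an analysis plan not shown.** This is fair, and their absence from the article is not in itself a fault. The point rests on the stated choice of matching variable and its stated reliability.

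**Conclusion.** The point holds in a limited form. Matching on this RAPM version controls intelligence only partly: at 50 per group the residual true difference has an SD of about 0.13, roughly twice that of a measure with reliability 0.91. The consequence is some loss of precision and an overstated claim of matching on intelligence. It is not systematic bias and does not invalidate the trial. At r = 0.3 to 0.5 the shift in an outcome has an SD of about 0.04 to 0.06, small beside a standard error of 0.20. The case for acting is that the remedy is nearly free and worth about 3% to 10% in effective sample size. These sizes depend on taking alpha as reliability, on one shared construct and on the assumed correlations.

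**What to change.** - Keep the matching algorithm and its variables unchanged.
- Report group balance on WASI Vocabulary and Block Design next to balance on RAPM, and describe the groups as matched on the RAPM score.
- Adjust the Training-versus-Control models for the matching variables (age, sex, RAPM, and Colour Shape Task switch costs in accuracy and reaction time) plus a WASI composite, for example the mean of the two subtest z-scores. For the RAPM outcome, use baseline RAPM as the intelligence covariate.
- Because analysts are not blinded, fix the composite and the covariate list before any group comparison is run.
- State in which session each WASI subtest is given. Any subtest given after allocation is still a pre-training measure, but it is administered by hand by staff who know the group, and the report should say so.

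The cost is a few model terms and one balance table. No new data are needed.

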### Concealment mechanism {16b}

Since the allocation sequence is generated using an algorithm, the group assignments are unpredictable and unknown to participants and experimenters until after the script is run. This takes place at least 2 weeks after the Baseline Cognitive Session. The group assignment is done once all participants of the same batch have completed the Baseline Cognitive Session. Prior to that, participants are assigned an enrolment ID that runs chronologically in the sequence of their recruitment. Hence, both experimenters and participants are unaware of participant’s group assignment until the allocation is completed.

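### As written, the 1:1 constraint in Sequence generation {16a} turns two-group minimisation into strict alternation, so random, matched and unpredictable allocation does not follow from it

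*Protocol article*

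**What the plan says.** Trial design {8} fixes the ratio: "The allocation ratio is set at 1:1 to ensure an equal distribution of participants between the two groups". It describes the method in these terms: "Group assignment follows procedures of a randomised controlled trial but with matching constraints of age, sex, intelligence, and baseline cognitive flexibility performance between groups".

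Sequence generation {16a} says that an R algorithm applies variance minimisation "while randomly allocating participants to either the Training or Control group". The matching measures are age, sex, the RAPM score, and the accuracy and reaction-time switch costs on the Colour Shape Task (CST). The steps given are:

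- The start: "Group assignment for the first recruitment batch is done sequentially upon initialisation of the algorithm".
- The switch to minimisation: "Once the number of assigned participants reaches the number of groups present, i.e. two in the present study", each later participant is tried in each group in turn.
- The criterion: the smallest sum of squared deviations of the group means from their common mean, found by "exploring all possible group allocation of a particular participant".
- The balance rule: 1:1 is kept by "constraining the algorithm such that it will not assign a new participant to the same group as the previous participant".

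The section concludes that the groups stay matched as batches are added. Concealment mechanism {16b} reasons that, because an algorithm generates the sequence, "the group assignments are unpredictable and unknown to participants and experimenters until after the script is run".

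**The concern.** The balance rule and the minimisation step cannot both operate. With two groups, a rule that excludes the last participant's group removes the choice that minimisation needs. The article describes no random start, random processing order or biased coin that would put chance back in.

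This trial depends on its allocation more than most. Trial design {8} and Outcomes {12} place inhibition, working memory and every cognitive flexibility task except the CST at post-test only, and Trial design {8} gives that as the reason why matching matters. The main efficacy comparison, under Evaluation of efficacy of Structure Learning training, is a post-test difference between groups and names no baseline adjustment. Baseline covariates are named only for the model relating training performance to cognitive flexibility. If the matching step is idle, the comparison lacks the safeguard on which the design says it relies.

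**Working it through.** **Inputs.** From the article: two groups; ratio 1:1; 60 per group, so N = 120 (Sample size {14}); five matching variables (age, sex, RAPM, two CST switch costs); the first two participants assigned sequentially; the criterion and constraint as above. Assumed for the simulation: the five variables are independent, four standard normal and sex 50/50 coded −1/+1; processing order is unrelated to them; 400 runs.

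**1. The stated ratio.** Strict alternation of 120 participants gives 60:60. The constraint does deliver the 1:1 ratio.

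**2. Choices left to the algorithm.** Admissible groups for each new participant = 2 groups − 1 excluded = 1. After the two initial assignments, 120 − 2 = 118 remain, and 0 of the 118 offer a choice. Coding the rule confirmed this: all 400 runs, with different covariates each time, produced one identical alternating sequence.

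**3. Expected balance without matching.** For a variable with SD 1 and 60 per group:

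- SD of the group difference = √(1/60 + 1/60) = 0.183
- mean absolute difference = 0.183 × √(2/π) = 0.183 × 0.798 = 0.146

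**4. Simulated balance, N = 120.**

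| Rule | Free choices of 118 | Mean absolute standardised difference | Mean of the largest of five | Runs with any variable > 0.2 SD | Size of one group |
|---|---|---|---|---|---|
| Constraint as written | 0 | 0.145 | 0.286 | 78% | 60 |
| Balanced random, no matching | not applicable | 0.149 | 0.290 | 79% | 60 |
| Constraint only within successive pairs | 59 | 0.039 | 0.078 | 0% | 60 |
| Minimisation, no size constraint | 118 | 0.022 | 0.043 | 0% | 4 to 114 |

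The first two rows agree with each other and with the 0.146 of step 3. Under the pair reading, the first member of each of the 118/2 = 59 later pairs is free and the second is forced. That keeps 60:60 and cuts the mean difference to 0.039/0.145 = 27% of its value under the stated rule. The last row shows that some size rule is needed, because minimising this criterion alone lets the groups become very unequal.

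**5. The claims against the rule.**

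- Random allocation: no chance element is described, and the rule is deterministic once the first group is set.
- Trying every possible group: only one is admissible.
- Groups kept matched: the matching data never affect an assignment.
- Unpredictable because an algorithm is used: under alternation, the position in the processing order plus the previous assignment gives the group.

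**The case against.** The strongest reply is that this is one sentence in a condensed article. The R script and the cited minimisation procedure are not shown. The code may apply the constraint only within successive pairs, which would fit the surrounding description, keep 1:1 and leave half the assignments free. It may also shuffle the order within a batch. The Abstract and Participant timeline {13} use the weaker label pseudo-randomised. This stands as a limit on what can be said about the trial as conducted. It does not repair the text, which says nothing of pairs or shuffling, and a shuffled order would restore chance but still leave the matching step idle.

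Second, alternation need not bias the comparison. The imbalance in the first row of the table is what ordinary balanced randomisation without matching gives. This also stands: what is lost is the extra matching, and comparability in expectation remains if order is unrelated to prognosis.

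Third, the usual danger of alternation is selective enrolment. Here the allocation is run only after a whole batch has finished baseline testing, at least two weeks after that session. That removes most of the opportunity. A reader might infer that allocation could be steered through the order of rows in the source file. The article says that enrolment IDs are chronological, but not that the script processes rows in that order, and it documents no such route.

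A reader might also suspect that the criterion is computed on raw units, so that one variable dominates. The article is silent on scaling, and the question is moot if the criterion never decides an assignment.

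**Conclusion.** The contradiction within Sequence generation {16a} holds and no other section resolves it. Read as written, the rule is strict alternation after the first assignment. The claims of random and matched allocation (Trial design {8}, Sequence generation {16a}) and of unpredictability (Concealment mechanism {16b}) therefore do not follow from it.

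The size of the loss is a mean absolute standardised difference of about 0.145, the level of unmatched balanced allocation, where a pairwise version of the same constraint would give about 0.04. These figures assume 120 participants, independent matching variables and a processing order unrelated to them.

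A reader might go further and conclude that the trial was in fact neither randomised nor matched. The article does not support that, because it does not show the code that was run. What it supports is that the described algorithm cannot do what is claimed for it, and that the actual one must be established.

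**What to change.** 1. Check the R script and state in Sequence generation {16a} the algorithm actually run, including the processing order and any random element.
2. For any batch still to be allocated, replace the constraint with one that leaves a choice and add a random element. Balance within pairs, balance within the batch, or a cap on the group-size difference would each serve. Dropping the constraint without a substitute is not an option, given the 4 to 114 range above.
3. If any batches were allocated by alternation, describe them as alternated and correct the wording in Trial design {8} and Concealment mechanism {16b}.
4. Adjust the post-test group comparisons for age, sex, RAPM score and both CST switch costs.

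The cost is small. Items 1 and 3 are text. Item 2 is a few lines of code, but Trial status projects the end of data collection for June 2023, so it may reach few participants or none. Item 4 uses data already collected at baseline and spends five degrees of freedom. It is the step that still protects the comparison whatever the script did. A cap on the size difference may leave the groups slightly unequal; balance within pairs does not.
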